### Primary outcomes in cross-sectional study

#### Physical activity and sedentarism

##### Self-report of physical activity and sedentarism

The INTA (in Spanish “Instituto de Nutrición y Tecnología de los Alimentos”) questionnaire will be used to evaluate the usual PA during the week (Monday to Friday) [57]. This scale is composed by 5 items or categories: i) sleeping time, ii) daily time on seated activities or in sedentary behaviours, iii) number of streets walked per day, iv) daily time participating in outdoor recreational activities, and v) time per week participating in exercise or scheduled sports. Each category scores from 0 to 2 points. The INTA questionnaire has shown good convergent validity properties and adequate test-retest reliability in Chilean schoolchildren [57]. Furthermore, Youth Activity Profile-Spain Latin America (YAP-SL) will be used. The YAP-SL is a Latin-American/Spanish adaptation of the 7-day self-administered recall questionnaire. This questionnaire has been translated by the PROFITH group (University of Granada, Spain) [51]. It includes 15 questions about activity at school, activity out of school, and sedentary behaviours.

##### Objective measurement of physical activity and sedentarism

PA and sedentary time will also be recorded through accelerometers, which allow an objective assessment of PA and sedentary time [58]. PA and sedentary time associations with brain and cognitive functions seem to be dependent on the instrument selected to estimate it (i.e., accelerometers vs. self-reports) [27]. Hence, triaxial accelerometers (GT3x, ActiGraph Manufacturing Technology Inc., USA) will be used to determine PA levels, sedentary time, and sleeping time during 24 h (7 days), as it has been recommended in a recent systematic review [58]. The accelerometer kit will be fixed to an elasticized belt and placed on the right side of children’s hip. At least 3 days of the week and 1 day of a weekend will be considered as a minimum recording time for valid registers. A valid day of PA will be considered when the accelerometer is worn for at least 10 waking hours. Accelerometers will be only removed during shower time or swimming activities. Besides, participants should register in a diary-log the time when they remove the device, go to bed, and wake up every day. Thereby, we will examine the time spent on light, moderate, and vigorous PA intensity, as well as sedentary time [59]. The total number of daily steps and steps per minute (i.e., cadence) will also be measured.

In addition, children will be encouraged to wear the accelerometers during the night in order to assess the time and quality of sleep, since it is well accepted that accelerometers provide a convenient way for sleep monitoring [60]. In this sense, the American Sleep Disorders Association supports the use of ACC in assessing several sleep anomalies such as circadian rhythm disorders, insomnia, and limb movements [61]. For all accelerometer data analyses, raw acceleration data will be acquired using ActiLife and then it will be processed using the GGIR analysis package (https://cran.r-project.org/web/packages/GGIR/) for the R programming language.

#### Physical fitness

##### Field-based physical fitness measurements

Physical fitness will be assessed through the ALPHA fitness test battery, which measures cardiorespiratory fitness by 20 m shuttle run test, speed-agility by 4 × 10 shuttle run test, and muscular fitness by handgrip strength, and standing long jump test [62]. To ensure an optimal performance, a brief demonstration of the technique and verbal instructions on how to perform each test will be carried out by researchers.

##### Self-reported physical fitness

Complementary physical fitness assessments will be carried out through the International Fitness Scale **(**IFIS) [63]. This instrument is composed by five items related to the perceived participants’ fitness in comparison with their friends’ physical condition, considering: i) overall fitness, ii) cardiorespiratory fitness, iii) muscular fitness, iv) speed-agility, and v) flexibility. The Spanish language version of IFIS is validated and shows an adequate test-retest reliability [64].

### Brain structure and function: magnetic resonance imaging (MRI)

Brain structural and functional information will be acquired using neuroimaging techniques. All images will be obtained with a 1.5 Tesla MRI scanner (AVANTO, Siemens Medical Systems, Erlangen, Germany). The acquisition protocols are:High resolution scanning: This provides structural information of the whole brain. T1-weighted images will be obtained with conventional sequence (MPRAGE, with TE/TR of 2.6/2200 ms), with 1.0 × 1.0 × 1.0 mm3 voxel size. This sequence will allow the study of each subject’s brain anatomy establishing associations between brain volumes and different health outcomes. Total duration of acquisition will be 4 min 32 s.Functional magnetic resonance in resting state (fMRI-rs): All fMRI images will be acquired with conventional gradient echo EPI sequence (TE/TR of 50/3000 ms), both fMRI-rs and fMRI-task. Slices will be positioned so that the entire brain is covered. This allows studying the resting state functional connectivity in the brain. Total duration of acquisition will be 6 min 08 s.Functional magnetic resonance in task (fMRI-task): Two different fMRI-tasks will be studied: one associated with working memory and another with verb generation. In both cases, the stimuli will be projected on a translucent screen that the child will see using the mirror positioned on top of the head coil that is used to acquire the MR signal. Stimuli will be generated with Python custom scripts, using OpenSesame [65], and words or letters will be presented randomly for each condition accordingly to the programmed design. Each task consists in:*Working memory n-back task.* Two different conditions will be performed (0-back and 2-back) [66]. In both cases stimulus will consist in black letters with font size sufficiently big for the child to read easily from within the magnet. For the sake of keeping the task simple, only 8 letters were used: ‘B’, ‘C’, ‘F’, ‘L’, ‘M’, ‘P’, ‘R’, ‘S’, and ‘X’ for the 0-back condition, where the participant will be asked to press an answer button whenever the “X” letter is displayed on the screen. The answer button will be held in the right hand of the participant. In the 2-back condition, subjects will be asked to press the button when the displayed letter is identical to the letter displayed two trials before, where a “trial” corresponds to the presentation of one letter. A total of four blocks (0-back and 2-back) will be performed, beginning with the 0-back condition. Each block initiates with a visual reminder of which task is about to take place: a white “X” letter over a blue background for the “0-back” condition and a black number “2” displayed over a red background for the “2-back” condition. Each block will consist in a sequence of 10 trials for condition; each letter is displayed during 500 ms, with an inter-stimulus interval of 2500 ms (a fixation cross will be shown during each interval). For both control and task conditions, the percentage of target trials is 40%. The total of correct answers will be recorded. The total duration will be 4 min 23 s.*Verb generation task.* Two conditions will be implemented: one without stimulus (control condition) and another with stimulus (active task-condition) [67]. In the control condition, a white screen will be presented during 30 s with a fixation cross in the center. While in the active task-condition, ten words will be showed, one at a time, each one presented during 3 s. The participants will be asked to think of a verb, or an action related to each word displayed in the screen. For instance, “bed” will be presented to induce a response such as “to sleep”, “to dream”, or another. All stimuli are presented in Spanish. Five runs of blocks (control–task) will be performed: total acquisition time will be 5 min 08 s.Diffusion Tensor Imaging (DTI): This sequence will allow to study the organization of structural (axonal) connectivity and to obtain a quantification sensitive to cytoarchitectonic organization of white and gray matter. 30 diffusion-weighting directions will be used, and with b values of 1000 s/mm^2^ the whole brain will be covered. Total procedure duration will be 4 min 02 s.

### Cognitive performance

#### NeuroCognitive performance test (NCPT)

The NCPT (Lumos Labs, Inc.) is used to assess cognitive performance [68]. It is a brief, repeatable, web-based platform of cognitive tasks intended to measure functioning across several cognitive domains including: working memory, visuospatial memory, psychomotor speed, fluid and logical reasoning, response inhibition, numerical calculation, and selective and divided attention. The NCPT has demonstrated adequate reliability and validity as a measure of cognitive performance, and in good concordance with pencil-paper assessments [68]. Eight cognitive tasks will be assessed in this study (Fig. 2): i) “Trail Making A” and ii) “Trail Making B” estimate attention, cognitive flexibility and processing speed, and are based on the Army Individual Test Battery [69] and the Halstead-Reitan Battery, respectively [70]; iii) “Forward Memory Span” and iv) “Reverse Memory Span” determine visual short-term and working memory, respectively, and are based on the Corsi Blocks tasks [71]; v) “Balance” based on Wechsler Intelligence for Children IV [72] and Piagetian Balance Beam Tasks [49], which judges for quantitative and analogical reasoning; vi) “Digit Symbol Coding”, based on the Digit Symbol Substitution Task [73] and evaluates processing speed; vii) “Go/No-Go” task that checks for response inhibition control and processing speed; and finally viii) “Progressive Matrices”, based on established matrix reasoning assessments [74] and is designed to assess problem solving and fluid reasoning.

**Fig. 2 Fig2:**
[figure not shown]
Eight cognitive tasks that conform the neurocognitive performance test

### Academic achievement

#### School grades

Final school grades will be obtained from the official records. The grades of mathematics, language, natural sciences, social sciences, English, PE, technological sciences, art and music will be consulted. Additionally, the grade point average (GPA) will be calculated.

### Secondary outcomes

#### Anthropometry

Initially, it will be performed with basic measures of weight (OMROM, HN-289-LA, Kyoto, Japan), height and seated height (SECA, model 213, GmbH, Germany); besides, waist, hip, and head circumference; and skinfold thickness of triceps, biceps, subscapular, suprailiac, and calf will be measured. Head, waist and hip circumference will be measured with an inextensible tape (Lufkin, Apex, NC). Waist circumference will be taken in a horizontal plane, at the level of the natural (minimal) waist and taken at the end of a normal expiration. Hip circumference will be measured at the maximum protruding part of buttocks at the level of the greater trochanter with children wearing minimal clothing, standing with their feet together.

#### Body composition

Electrical bioimpedance will be used to measure body composition, employing an Inbody S10 device (Biospace, Seoul, Korea). The participant will be seated, with eight electrodes placed in the body, two in each hand, and two in each ankle. Each participant will lay seated for a 5 min rest period before the procedure.

#### Maturity

The maturity status will be estimated through two methods. First, peak height velocity (PHV) will be calculated through Moore and colleagues’ equation [75]. Complementarily, Tanner staging will be used to assess the degree of pubertal development. The participant will select his/her state on a scale from 1 to 5 maturity degrees.

#### Digit ratio

Recently, length of fingers, and specifically the ratio of the second and fourth digits of the hand (2D,4D) has been strongly related to prenatal testosterone exposure [76]. We included this measurement due to the relationship of testosterone with brain development and the association of 2D:4D with brain volumes and intelligence quotient [77, 78]. Therefore, this novel and simple measure will be calculated according to criteria of digit ratio measurement guide [79]. Finally, analyses will be made with Autometric software whose reliability has been previously demonstrated [80].

#### Blood pressure

Resting blood pressure will be assessed after 5 min of rest by an automated device (Omron HEM-7130®). Two readings will be taken with a difference of 3 min between each one. With the participant seated, left arm will be placed on the table and the bracelet will be fitted around the arm, above the elbow, and aligned with brachial artery. A pediatric bracelet will be used when necessary.

#### Heart rate variability

Prior to MRI, an objective estimation of autonomic balance will be measured through the heart rate variability (HRV). Participants will be placed in a quiet room without noise or any other distracting stimuli (e.g., light) and HRV will be measured completely at rest in a supine position. A minimum of 12 min of recording is needed. A practical finger device, SENSECORE, which has shown good reliability and accuracy in children will be used [81]. Analysis will be made using the Kubios HRV software (University of Eastern Finland, Finland) [82].

#### Sleep self-report (SSR)

Sleep patterns will be assessed using the **sleep self-report** [83]. This questionnaire is composed by 26 items and four subscales: 1) Sleep quality; 2) Sleep anxiety; 3) Bedtime refusal; and 4) Sleep routines. The Spanish version showed adequate psychometric properties and good internal consistency (w = 0.85) [84].

#### Mode of commuting

Commuting to and from school will be evaluated by self-report. Participants will answer the following questions “How do you usually travel to (from the) school?”, “How many distance there is between home and school?” and “How much time does it take to get to (from the) your school?”. The responses to the first question can be: by walk, bike, motorbike, car, bus, several transports or other transports (requesting it in those cases). These questions come from the previously validated “PACO” (in Spanish “Pedalea y Anda al Colegio”) questionnaire [85, 86].

#### School context physical activity

The school PA questionnaire (SPAQ) is a Chilean validated questionnaire referred to different aspects of school environment and PE lessons [87]. Questions refer to sport practices, possibilities of outdoor environment, body expression development, PA promotion, development of self-care, development of active life, didactic of lessons and any kind of other school activities.

#### Dietary patterns

In order to estimate quality of nutritional intake and nutritional habits two food frequency questionnaires will be used: the Mediterranean Diet Quality Index (KIDMED) for children [88] and the Healthy Eating Index (HEI) according to national guidelines [89]. Also, questions about quality of breakfast will be performed. The KIDMED index has been previously validated and it is widely used in childhood [88].

#### Health-related quality of life

Kidscreen-27 questionnaire will be used to measure health-related quality of life [90]. This questionnaire was designed specifically for young people aged 8–18 years and consists of 27 items and five dimensions: i) physical well-being, ii) psychological well-being, iii) its relationship with parents and children autonomy, iv) social support and peers, and v) school environment. The Chilean version of Kidscreen-27 has shown an adequate internal consistency (*α* = 0.89) and high reliability [91].

#### Daily stress in the school context

A scale of stress will be used to assess the daily stress within the school context. This instrument consists of 18 items, arranged in 3 dimensions: i) stress of relational violence, ii) academic stress, and iii) environmental stress. The validation of this scale has shown good internal consistency (*α* = 0.90) and adequate validity properties in Chilean children and adolescents [81].

#### School characteristics

Several characteristics of school will be registered such as SVI, scholar schedule, public or private administration, location, and educative project.

#### Parental reports

Also, through self-report from parents we will obtain different variables such as family socioeconomic status, nutritional status, parents’ educational level, height and weight of participant at birth, possible complications during pregnancy or at birth and other sociodemographic information. Additionally, parents will fill the Children’s Body Image Scale (CBIS) for preadolescent and children according to their own perceptions about their children.

### Design of cross-over acute trial

The design of the second part of the project will consist of a cross-over trial where the participants will perform, on different days, three different PA protocols with equal energy expenditure fashion in a random order. Before starting this part, schoolchildren will be evaluated by a physician (preparticipation physical evaluation), under previous authorization of their parents. The examination will consist in the realization of a complete clinical history and a general physical examination, with the purpose of verifying their health status and avoiding possible injuries or illnesses during PA protocols. Any adverse events occurring during the trial will be documented and submitted to the physician, which will analyze the exclusion of the participant from the trial.

Each child will visit our laboratory three times, every 2 weeks to ensure a “wash-out” period with the purpose of mitigating the PA effect from each protocol. The order will be determined using a computer-generated ordering system. The random sequence was generated by the web-based Research Randomizer (randomizer.org). A staff member responsible for recruitment will perform randomization. Participants will assist to the three different sessions at the same weekday (e.g., Monday) and at the same daytime to avoid differences in preceding school activities or circadian rhythms [82]. Participants will undergo a “Sedentary condition” (SC), sitting and watching a documentary on TV as has been used previously [82], and two different PA protocols consisting in “Moderate-Intensity Continuous Training” (MICT), continuous outdoor brisk walking/running; and “Cooperative High-Intensity Interval Training” (C-HIIT), composed of a circuit training with a partner (physical education teacher) (Fig. 1). These three protocols have been chosen in view of what corresponds to types of activities usually performed in schools. Thus, SC mimics the time spent during any academic lesson (i.e. mathematics or language lessons); MICT represents the typical activity in a PE class; and C-HIIT has been selected since it is postulated as an exercise protocol that could possibly be implemented in thethe PE class [92]. The three protocols are designed so that energy expenditure is equivalent between them, to eliminate differences in the energy expenditure as a possible confounding factor. Thus, the duration will be different among protocols.

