**Fig. 1 Fig1:**
[figure not shown]
Cross-sectional and cross-over RCT study design

During the first part (i.e., cross-sectional study), measurements will take place in public and private schools, with two visits of 4 h each separated by 8 days. At the first visit, questionnaires, cognitive performance and anthropometric measurements will be assessed, followed by accelerometers placement. During the second visit, physical fitness and other questionnaires will be evaluated, plus accelerometer removal. A detailed description of all evaluations can be found in the measurements section.

Regarding the second part (i.e., crossover-randomized trial), children will be randomized to each protocol session, participating in all of them with two-weeks apart. Thus, they will assist to our gym to perform one of the three protocol and subsequently they will be move to a laboratory where they will undergo EEG and eye-tracking measurements during resting state condition and during two different cognitive tasks. More details can be found in following sections.

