##### C-HIIT

Each adolescent together a personal trainer will do a circuit training based on a collaborative fashion. The specific protocol has been published previously [92]; in brief, it consists in four series of four cooperative exercises which combining cardiorespiratory, speed–agility, and coordinative training exercises because these are the fitness components that mostly enhance cognitive capacity in adolescents [56, 92, 96]. The session will be organized with work-to-rest ratios of 20:40 s. Both, MICT and C-HIIT protocols include a short 4 min warm-up (running, sideways movements and dynamic stretching at medium intensity) and 4 min of cool-down. The C-HIIT protocol must be done to high intensity, corresponding to ≥85% of maximum heart rate [97].

After each PA protocol, the participants will undergo EEG and eye-tracking measurements as follows: 1st, resting state spontaneous brain activity will be assessed during 3 min with EEG only, and subsequently, eye-tracking will be registered in parallel with EEG while participants perform the cognitive tasks (a working memory task and a reading task). The measurements will start between 20 to 25 min after the end of each condition. In this way, we will emulate a school recess in the Chilean context, before the start of the next subject. All measures will be carried out in the “Laboratorio Lenguaje & Cognición ELV”, which belongs to the Literature and Language Sciences Institute of the Pontificia Universidad Católica de Valparaíso. To avoid subjective influence of evaluator, when the participants go to the laboratory, the evaluator will be blinded according to which PA protocol participants performed.

Regarding optimize participant retention, parents or legal guardian will be contacted and reminder by phone calls, or email when the participant loses any of the three scheduled sessions. Then, missed sessions will be reprogramed according to availability of participants and respecting study design. An inventory of each section of this trial is available in the SPIRIT checklist (Additional file 1).

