#### Reading task

Language processing will be assessed by a reading comprehension task where short paragraphs will be presented to be read normally. The eye-tracking technique will be employed to record eye position, movement and pupil diameter, simultaneous to the EEG record. Participants will seat in front of a monitor, at approximately 60 cm, placing their chin on an ergonomic stand piece, which helps to decrease head movements and improves eye-tracker signal precision. The reading task will be presented with the latest version of Tobii Pro Lab. After calibrating the system, each child is given a brief contextualization of the topic, before they start to read, knowing that later they will be asked seven comprehension questions with varying degrees of complexity. The participants must indicate the correct answer among four alternatives. It should be noted that three literary texts will be used, presented in a random fashion (1 per exercise condition). These texts will have the same difficulty, the same distribution of areas of interest, similar amount of words, and will be previously validated by a panel of experts. The reading of each word is expected to generate an EEG negative potential with latency close to 400 ms (N400). The amplitude, topographic distribution and latency of this potential are electrophysiological neuromarkers of linguistic ability in general, and the ability to construct meaning from words [103]. The eye-tracker will be used to study the ocular trajectory during reading and establish the moments when words are read. EEG and eye-tracking will be registered simultaneously to record eye movements related to reading, giving measures such as reading speed, fixation durations, number of fixations, among others), and to measure eye fixation related EEG potentials associated with cognitive load while reading words [50]. The reader should note that this potential coincides experimentally with the N400, so they may represent different brain processes superimposed, or be essentially the reflection of the same mechanism.

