#### Working memory performance

Hits, misses, omissions, and accuracy will be calculated for targets and non-targets of the n-back task, as well as response latency.

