#### Cross-over study

Differences among condition will be calculated using general lineal models (95% confidence) and estimating the Hedges effect size [115]. Strength of effect will be assessed according to the following interpretation: trivial (0–0.19), small (0.20–0.49), medium (0.50–0.79) and large (0.80 and greater) [116]. The significance threshold analyses will be *p* < 0.05.Regarding missing data, it is anticipated that missing data could be due to faults in the EEG and eye-tracker, and thus will be missing at random. For this reason, multiple imputation will be used to address this issue.

In addition to performance in the task of working memory and reading, several neurocognitive variables (amplitude and latency of both potentials, frequency of the alpha wave, and variation of its amplitude with the opening of the eyes) will be studied statistically using a model of mixed effects, which initially will use the factors: subject, exercise protocol and cognitive ability (high or low performer). Subsequently, it will be extended to other factors (the rest of the measures of the Cogni-Action Project, such as body composition, sexual development status, anthropometric measures, socioeconomic, brain structure, etc.), to establish which factors and interaction between them have greater statistical significance in the acute effects of PA on cognitive and academic performance.

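### The recruiter also allocates the order of conditions from a pre-generated sequence with no stated safeguard, so the order could be foreseen or steered; this is a conditional risk, mainly for the repeated n-back

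*Protocol article*

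**What the plan says.** All three conditions are given to every boy: "children will be randomized to each protocol session, participating in all of them with two-weeks apart" (Design and participants, text under Fig. 1). Only the order is random. The section Design of cross-over acute trial covers three things:

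- How the order arises: "The order will be determined using a computer-generated ordering system".
- Where the list comes from: "The random sequence was generated by the web-based Research Randomizer (randomizer.org").
- Who applies it to the boys: "A staff member responsible for recruitment will perform randomization".

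The generation of the sequence is in the past tense and the act of randomising is in the future tense. The natural reading is that a finished list is applied by the person who recruits.

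The only blinding stated is at the laboratory, where "the evaluator will be blinded according to which PA protocol participants performed" (C-HIIT section). The article does not say who holds the list, how an order is released, or whether the six possible orders are balanced.

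Two further passages decide how much this matters. For the n-back, "Hits, misses, omissions, and accuracy will be calculated for targets and non-targets of the n-back task, as well as response latency" (Working memory performance, a primary outcome); the task follows each condition, so each boy does it three times. For reading, "three literary texts will be used, presented in a random fashion (1 per exercise condition"). The mixed model is one "which initially will use the factors: subject, exercise protocol and cognitive ability (high or low performer") (Data analysis plan, Cross-over study). The later extension adds other measures of the project, such as body composition and socioeconomic status. Session number is not named.

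**The concern.** Keeping recruitment and allocation apart stops anyone from fitting the next allocation to the next participant. Here the article gives both tasks to one person and describes nothing that keeps the coming order from that person. This is a role that the article fixes, not a detail that it leaves out.

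In a cross-over, foreknowledge cannot change which conditions a boy receives. It can change when he receives them. Timing matters for a task that improves with repetition: a condition that tends to come late collects the practice gain. With no balancing of orders stated and no session term in the initial model, an unsteered random order is the main stated protection of the n-back contrasts against practice. The reading task is less exposed, since each condition has its own text.

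**Working it through.** **Inputs from the article.** 32 boys, three conditions, six possible orders, design difference 71.50 ms, SDs 93.1 and 91.6, loss 20% (Cross-over study, Total sample size and power).

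**Assumed, not in the article.** Response latency falls by g ms per session through practice. Where one value is needed, g = 20 ms with a between-boy SD of 10 ms; the range shown is 10 to 40 ms.

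**The plan's own figure.** Pooled SD = √((93.1² + 91.6²)/2) = 92.35. Two-sided α 0.05 (sidedness assumed) and power 80% give n = 2 × (1.960 + 0.842)² × (92.35/71.5)² = 26.2, so 27 per group. Allowing for loss, 27 × 1.2 = 32.4 or 27/0.8 = 33.75, close to the stated 32. The point here does not depend on this figure; 71.5 ms serves only as a yardstick.

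**Step 1: swapping boys on a fully used list.** Let k be the session of C-HIIT minus the session of SC, so k is −2, −1, +1 or +2. Practice adds −g × k to a boy's C-HIIT minus SC latency. If boy A (k = +2) and boy B (k = −2) exchange positions, the total moves from −2gA + 2gB to +2gA − 2gB, a change of 4(gA − gB). With a common gain the change is zero. A boy's baseline level cancels within him.

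**Step 2: simulation of step 1** (30 boys, five per order, g mean 20 and SD 10 ms):

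| How boys meet orders | Mean shift in C-HIIT minus SC |
|---|---|
| No matching | about 0 ms |
| Matched on baseline level | about 0 ms |
| Matched perfectly on individual practice gain | −12.6 ms |

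The last row is an extreme. It requires knowing each boy's practice gain in advance.

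**Step 3: positions skipped or overridden.** If SC precedes C-HIIT in a share p of boys, and the three orders in each direction are equally used, the mean gap within a direction is (2 + 1 + 1)/3 = 4/3 sessions. The shift is −(2p − 1) × (4/3) × g:

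| p | g = 10 | g = 20 | g = 40 |
|---|---|---|---|
| 50% | 0 | 0 | 0 |
| 60% | −2.7 | −5.3 | −10.7 |
| 75% | −6.7 | −13.3 | −26.7 |
| 100% | −13.3 | −26.7 | −53.3 |

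All entries are in ms. Neither p nor g can be read from the article.

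**Step 4: chance alone.** If orders are drawn independently with no balancing, the practice-related SD of the contrast for 30 boys at g = 20 (SD 10) is √(2 × (20² + 10²)/30) = 5.8 ms. With five boys per order it is √(2 × 10²/30) = 2.6 ms. Simulation gives the same values. A session term is therefore useful even when nobody steers.

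**The case against.** The strongest defence has four parts.

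- **Concealment.** A reader might infer that the order is known to be unconcealed. The article does not say so: it never states that the recruiter sees the list or knows the next entry. It is a condensed account and refers to a SPIRIT checklist in an additional file that is not at hand. This stands. Only the joining of the two roles, without a described safeguard, is on the page.
- **Bias.** A reader might infer that the contrasts are therefore biased, for instance by booking less fit or hesitant boys so that C-HIIT comes last. Steps 1 and 2 show that such matching on a fully used list adds nothing under a common practice gain. This stands too. Bias needs unequal use of the orders or matching on individual gain, which a recruiter could hardly know before the first session.
- **Opportunity.** Consent is obtained at group meetings, a physician examines the boys beforehand, and sessions keep the same weekday and time of day at two-week intervals. This narrows the room for steering but does not close it, since missed sessions are rebooked around the boys' availability.
- **Loss.** A reader might infer that a late C-HIIT session would be the one most often missing. The 20% is an overall loss rate, missed sessions are rescheduled, and multiple imputation is planned. Nothing in the article shows loss that differs by condition.

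The defence does not remove the sentence itself, which assigns allocation to the recruiter.

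**Conclusion.** The point holds as a conditional risk. The article gives allocation from a pre-generated sequence to the person who recruits and describes no safeguard, so the order could be foreseen or steered. This alone does not bias comparisons between conditions. It could do so for the n-back if list positions were skipped or overridden, or if orders were matched to practice gain, and the initial model has no session term to absorb the first of these.

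The size cannot be derived from the documents. One purely illustrative case of overriding the list is a boy moved from C-HIIT first and SC last to the opposite order without a compensating swap. His session gap changes by 4, so the contrast shifts by 4/32 = 0.125 of one session's gain. For five such boys, a number with no source, and an assumed 10 to 30 ms, that is 6.3 to 18.8 ms, or 9 to 26% of 71.5 ms. A reader might take this as the expected bias. The documents do not support that, because both the count and the gain are invented and matching boys to a fully used list does not produce it.

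**What to change.** Replace the sentence on who randomises. An existing team member who does not recruit, schedule or test holds the list. That person releases each boy's order in strict list sequence, with a log entry, only after four steps are complete: consent, the physician's examination, confirmation of eligibility, and booking of his three dates. If the full protocol or the SPIRIT file already names an independent holder, the article's sentence should be reconciled with it.

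Add session number (1 to 3) as a factor in the cross-over model. It absorbs a common practice gain when orders are uneven, whether by steering or by chance. It does not correct matching on individual gain, so it complements the change in roles and does not replace it.

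Cost: one task is reassigned within the team, a log is kept, exercise staff learn each boy's condition later, and the model carries two more parameters. The sample size does not change.
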